
## Description of the Research Project

### Hypothesis to be tested:

In a hypothesis testing research proposal, briefly mention the hypothesis to be tested and provide the scientific basis of the hypothesis, critically examining the observations leading to the formulation of the hypothesis.

Does this research proposal involve testing of hypothesis: ☐ No ☒ Yes (describe below)

We hypothesize that it is feasible to train GoB staff at District, Sub-district, Union and CC levels and integrate ECD activities in CCs in Bangladesh and thereby improve malnourished children's development after a year of intervention.

### Specific Objectives:

Describe the specific objectives of the proposed study. State the specific parameters, gender aspects, biological functions, rates, and processes that will be assessed by specific methods.

General objective is to establish a sustainable programme whereby ECD activities are integrated into the routine activities of CCs in rural Bangladesh for undernourished children and national, district, sub-district, and union level trainers are developed to train clinic staff.

The specific objectives are:

1. To establish a mechanism for sustainability at central, district and sub-district levels: including training , supervision, monitoring and reporting
2. To assess the feasibility of the sustainable model including:
  - a) Coverage: Assess number of children participating in the programme

- b) *Compliance* of inspectors and clinic staff
  - i. Attendance at training,
  - ii. % of sessions run,
  - iii. % of sessions observed by inspectors
- c) *Fidelity*:
  - i. % of inspector reports correctly filled in
  - ii. % of sessions meeting acceptable standards
- 3. To assess the impact on maternal knowledge and depressive symptoms, stimulation in the home and child growth, cognition and language in a subsample

### Background of the Project including Preliminary Observations:

Provide scientific validity of the hypothesis based on background information of the proposed study and discuss previous works on the research topic, including information on sex, gender and diversity (ethnicity, SES) by citing specific references. Critically analyze available knowledge and discuss the questions and gaps in the knowledge that need to be filled to achieve the proposed aims. If there is no sufficient information on the subject, indicate the need to develop new knowledge.

Global child development: Approximately 250 million children under 5 years of age in developing countries do not reach their full potential due to poverty, malnutrition and lack of a stimulating environment (Black et al. 2016). In Bangladesh, all the above risks are prevalent and many children are exposed to several risk factors at a time that have cumulative effects on their development. Almost half of the children under 5 years of age suffer from some form of malnutrition. It is also a low middle income country and one of the most densely populated in the world. A recent study showed that poor Bangladeshi children showed a significant cognitive deficit as early as 7 months of age compared to more affluent children and the deficit grew bigger as children reached 5 years of age (Figure 1).

[figure not shown]

In early childhood, parenting practices tend to be poor and the quality of stimulation in the home is very limited with few children having access to toys or books and parents playing and chatting with them. At least half the children in Bangladesh are therefore disadvantaged and among them, undernourished children are most at risk of poor development and require additional interventions. The Child development unit (CDU) at icddr, b in Bangladesh has modified the Reach-Up curriculum, a comprehensive curriculum of psychosocial stimulation and play and tested it for underprivileged children in six studies ([name] et al. 2006; Nahar et al. 2009; 2012; Tofail et al. 2013; Tofail et al. (2)- in preparation). In all the studies we consistently found significant benefits to children's development and behaviour.

More recently we conducted two large cluster randomized controlled trials in 130 community clinics (CCs) where we adapted the same curriculum for small groups of mothers and children to be run at 65 CCs ([name] et al. 2019; Mehrin et al. in preparation). In these studies, we introduced the early childhood development (ECD) and nutritional counselling programme for malnourished children aged 6-24 months and compared them to children in 65 control CCs. Mothers with their children attended sessions at the clinic every two weeks for one year. In the first study mothers attended in pairs ([name] et al. 2019) and in the second one they attended in small groups (Mehrin et al. in preparation). To develop a sustainable model, we trained the Government's staff working in CCs to provide ECD intervention for undernourished children as part of their routine work. The studies showed substantial and comprehensive benefits to children's development and behaviour.

Qualitative research found most mothers and providers were satisfied with the programme and were willing to continue if the programme continued further.

## Research Design and Methods

Describe the research design and methods and procedures to be used in achieving the specific aims of the research project. If applicable, mention the type of personal protective equipment (PPE), use of aerosol confinement, and the need for the use BSL2 or BSL3 laboratory for different part of the intended research in the methods.. Define the study population with inclusion and exclusion criteria, the sampling design, list the important outcome and exposure variables, describe the data collection methods/tools, and include any follow-up plans if applicable. Justify the scientific validity of the methodological approach (biomedical, social, gender, or environmental). Also, discuss the limitations and difficulties of the proposed procedures and sufficiently justify the use of them.

This proposal will cover the first phase of the intervention implementation and we will set up a work plan with all necessary supports for the second phase (e.g. manualised curriculum, instruments for observing visits, training manual, and system for producing play materials as well as trained master trainers), incorporating any lessons learnt from the 1st stage.

### 1st stage: Implementation trial

#### *Inclusion criteria:*

- Moderately and severely malnourished children aged 6-24 mo of both sexes and whose parents consent to participate in the programme.
- Mid-upper arm circumference (MUAC) < 12.5 cm will be used to define malnutrition
- Routes of identification of eligible children:
  - A. At sub-district level
    - a. Children attending integrated management of childhood illnesses (IMCI) corners
    - b. Children attending treatment centres for severe acute malnutrition
  - B. At Union level
    - a. Children attending family welfare centres (FWCs)
  - C. At village level
    - a. Children attending immunization centres
    - b. Children attending community clinics (CCs) for illness or immunization

#### *Exclusion criteria:*

- Children with MUAC > 12.5 cm
- Those whose parents do not consent to participate
- Children with disability, multiple births or any congenital abnormality will be included in the intervention but excluded from the evaluation sample.

Simultaneous with the training, we will identify the eligible children.

#### *Selection of area:*

We have selected Sylhet and Rangpur Divisions based on high prevalence of malnutrition in those areas. From each Division, we have selected 2 districts; hence we will be working in 4 districts. We have dropped the City corporation sub-districts and will have 13 sub-districts in Sylhet (Hobigonj & Moulvi Bazar) and 8 sub-districts in Rangpur (Rangpur & Thakurgaon). We therefore aim to target 21 sub-districts with a total number of 554 CCs. These CCs are supervised by approximately 418 supervisors (Family Planning Inspectors, Health Inspectors and Assistant Health Inspectors) and are run by approximately 1600 health staff in rural areas, all of whom will receive training. We expect to enrol approximately 40 children per clinic.

## Procedure

We will work with the Ministry of Health and Family Welfare (MOHFW) and the Ministry of Women and Children Affairs (MOWCA); the two leading ministries for ECD in Bangladesh. We will recruit and train 3 Master Trainers at national level. Through a cascade of training they will train and develop a pool of trainers of trainers (TOT) in each of the 4 districts in consultation with the 'Civil Surgeon' (CS) who is the highest health administrative personnel in a district. We have identified possible personnel at district level, based on their time availability, skills, remaining length of service and educational level, but there may be different personnel at each district, therefore we will consult with each CS before selecting persons for training. The possible candidates at this level are:

1. District health education Officers (DHEO) (1 senior and 1 junior )
2. Public Health Nurse
3. Assistant Director, Clinical Contraceptive (ADCC)
4. Medical officer under CS (MOCS)
5. Medical Officer, Disease Control (MODC)
6. District Shishu (child) Academy Officer

In each district we will have a pool of 5-6 TOTs from the above, based on the recommendation of the CS, however, all of them including the CS will be given a one-day orientation on the programme.

### Training:

In previous studies we have conducted several training programmes for Government and NGOs and have expertise in training trainers. Training for the present study will follow a cascade model from Master Trainers (MT) down to clinic staff (Figure 2).

#### *Training of trainers:*

Training will be most extensive at the district level for the TOTs and will include the following:

- Curriculum of ECD activities and nutrition education (5 days)
- Training and mentoring procedures including observing play sessions, managerial and facilitation capacity (1-2 days) for monitoring of training by TOTs and program implementation by health staff in the CCs.

The MTs will each go to one of the districts and train 5 or 6 district TOTs. The district TOTs will be trained in a single group, but there will be hands-on training or individual coaching in order for everyone to practice what is required for such training.

Figure 2. Cascade of training

[figure not shown]

The district TOTs will then be given a schedule to train the next level of TOT at the sub-district level and will be coached by the MTs until they reach acceptable standards.

For the sub-district level of TOT we will consult with the sub-district health and family planning officer and sub-district family planning officer and identify 8 TOTs among the health officers and inspectors in the sub-district. We will have varying number of TOTs in each district, based on the number of sub-districts. The district TOTs will start training at sub-district level in 2-3 phases based on the number of trainees. Our MTs will accompany and observe the training to ensure quality and coach as necessary as the sub-district trainers are trained, they will plan a schedule for the training of the CHCPs, HAs and FWAs in each sub-district. We will request the district TOTs to be present at their training sessions to again ensure the standard of the training. This will result in a high level of training provided to field staff and reduce dilution of the programme.

The research team will pilot the use of training materials before the actual training to ensure its suitability and user-friendliness and to identify any challenges that require handling to ensure that we can hand over the training to the govt. trainers. All these challenges will be recorded and considered for the future training programmes. Each training batch will consist of 15-20 trainees according to the number of trainers in each sub-district.

*Training of the clinic workers:* The final level of training will be training of the CHCPs, HAs and FWAs and will comprise of:

1. The curriculum of psychosocial stimulation and nutrition

2. Relating to mothers and children and empowering mothers
3. Procedures in conducting group sessions
4. Reporting procedures
5. Placing requisitions, storing and maintaining toys and books at the CC.

### Sample Size Calculation and Outcome (Primary and Secondary) Variable(s)

Clearly mention your assumptions. List the power and precision desired. Describe the optimal conditions to attain the sample size. Justify the sample size that is deemed sufficient to achieve the specific aims.

**Sample size for the evaluation sample:** is calculated using a matched case-control design and effect size of 0.3 SD. We will select 10 children from 40 intervention and 40 control CCs. The control CCs will be the waitlisted CCs in the neighbouring districts of the same Divisions, where intervention has not started yet. The undernourished children will be identified by the research staff and asked to participate in the study. There will be 640 children required for the evaluation. We will add 25% to the sample size to account for losses during the study. Therefore, a sample of 800, 400 in each group will be sufficient to evaluate the study.

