| (1) Undernourished intervention                                                                                                                                                                                                                                                                                                                                                                                                                                                                                                                                                                                                                                                                                                                                                | 388                                                                                                                                                                                                                                                                                                                                                                                                           | (3)                      |            |
| (2) Undernourished control                                                                                                                                                                                                                                                                                                                                                                                                                                                                                                                                                                                                                                                                                                                                                     | 388                                                                                                                                                                                                                                                                                                                                                                                                           | (4)                      |            |

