|                                                                                                                                                                                                                                                                                                                                                                                                                                                                                                                                                                                                                                                                                                                                                                                |                                                                                                                                                                                                                                                                                                                                                                                                               | Total sample size | 776 |
| Determination of Risk: Does the Research Involve (Check all that apply)                                                                                                                                                                                                                                                                                                                                                                                                                                                                                                                                                                                                                                                                                                 |                                                                                                                                                                                                                                                                                                                                                                                                               |                          |            |

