| Field Research Officers (training & quality)                                      | GS5- CSA     | 641        | 2        | 100%                               | 6      | 7,692          | 10,073         | 705            | 100%       | 10   | 14,102         | 18,467         | 21,794         | 28,539           |
| Field Research Officer                                                            | GS5-CSA      | 641        | 1        | 100%                               | 6      | 3,846          | 5,036          | 705            | 100%       | 2    | 1,410          | 1,847          | 5,256          | 6,883            |
| Field Research Assistant                                                          | GS3-(CSA)    | 419        | 6        | 100%                               | 6      | 15,066         | 19,729         | 460            | 100%       | 2    | 5,524          | 7,234          | 20,590         | 26,963           |
| Bayley Tester (FRA)                                                               | GS3-(CSA)    | 419        | 2        | 100%                               | 6      | 5,022          | 6,576          | 460            | 100%       | 5    | 4,604          | 6,028          | 9,626          | 12,605           |
| Senior Field Assistants                                                           | GS2-CSA      | 348        | 2        | 100%                               | 8      | 5,566          | 7,289          | 383            | 100%       | 12   | 9,185          | 12,027         | 14,751         | 19,317           |
| Data management Supervisor                                                        | GS4/11       | 1,038      | 1        | 100%                               | 8      | 8,304          | 10,874         | 1,142          | 100%       | 12   | 13,702         | 17,942         | 22,006         | 28,817           |
| Office/Field attendant                                                            | GS2/2-FT     | 535        | 1        | 100%                               | 8      | 4,280          | 5,605          | 589            | 100%       | 12   | 7,062          | 9,248          | 11,342         | 14,852           |
| Field Organizer (Office)                                                          | SP level     | 140        | 3        | 100%                               | 8      | 3,348          | 4,384          | 153            | 100%       | 12   | 5,524          | 7,234          | 8,872          | 11,618           |

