### Budget Justifications

Please provide one page statement justifying the budgeted amount for each major item, including the use of human resources, major equipment, and laboratory services.

**Personnel:** [name] is the project lead. She will dedicate almost 30% of her time to the implementation and full conduct of the project. [name]; the Co-PI of the project will spend 15% of her time. She will help in manual development and visiting Health officials, motivating their staff, analyzing data and drafting manuscripts. [name] will spend 30% of his time to help in implementing intervention and liaison with Govt. Stakeholders. [name], will develop the training curriculum for the Group Intervention and will also help in data analyses and manuscript writing. [name] will help in planning this scale-up project. She will provide advice on how to go forward and how to trouble-shoot. She will also help in data analyses and manuscript writing. Two Senior Research Investigators will work part time on this project and will be in charge of communicating with the GOB and maintaining a close liaison with the Ministries. There will be 3 master trainers (RIs), who will organize the trainings and observer and coach the health officers. In addition GCC requires Liaison member who will keep close contact with the GoB as well as GCC. The two research investigators will be in charge of test supervision and intervention implementation. There will be 1 senior Research Officer and 2 Research Officers responsible for trainings, quality control of intervention. In addition we need 6 junior facilitators who will be working at the field and keep track of all the stimulation activities as well as arrange logistics. We need 4 testers to perform Bayley test and anthropometry twice on 1200 children in the study. One data management supervisor is required for data entry and cleaning. Five Field Organizers are required to maintain liaison with CCs and are required to run errands like delivering letters to the ministries, collecting materials for tests, photocopying questionnaires, etc.

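### The protocol gives three unreconciled totals for the evaluation sample (776, 800 and 1200), and only 800 follows from its stated inputs

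*Protocol*

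**What the plan says.** Three parts of the protocol give a total for the children who will be evaluated.

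- **Sample Size Calculation and Outcome Variable(s).** The sample "is calculated using a matched case-control design and effect size of 0.3 SD". The sampling plan is: "We will select 10 children from 40 intervention and 40 control CCs". The pre-loss requirement is: "There will be 640 children required for the evaluation". After 25% is added for losses, the section ends: "Therefore, a sample of 800, 400 in each group will be sufficient to evaluate the study".
- **Application form, table of the proposed sample size for evaluation.** The undernourished intervention and undernourished control rows each show 388, the two remaining subgroup rows are blank, and the total reads "Total sample size | 776".
- **Budget Justifications, Personnel.** "We need 4 testers to perform Bayley test and anthropometry twice on 1200 children in the study". The personnel line for Bayley testers in the budget table that is visible shows 2 posts.

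**The concern.** All three totals appear to describe the same children. The form's table is labelled as the evaluation sample, the sample size section is about the evaluation sample, and the budget sentence concerns Bayley testing and anthropometry, which are on the list of outcome measures. The Project Summary and Specific Objectives confine child development assessment to a subsample, and no further tested group is described that would account for the difference between 800 and 1200.

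The number to enrol governs recruitment, consent and tester workload, and it is the yardstick for saying later whether the evaluation was completed as planned. With three figures in current text, the form submitted for approval, the design and the resourcing do not agree. A reader of the form alone would call the evaluation complete at 776, and a reader of the sample size section would call it 24 short.

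**Working it through.** **Inputs.** From the sample size section: 640 evaluable children (320 per group), 25% added for losses, 10 children per clinic, 40 + 40 clinics. From the application form: 388 per group. From the budget justification: 1200 children, each tested twice. Significance level, power and intracluster correlation (ICC) are not stated there, so 640 is taken as given.

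**1. The protocol's own figure.** 640 × 1.25 = 800, and 10 × (40 + 40) = 800, which is 400 per group. Both routes agree, so 800 is reproduced exactly.

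**2. The other two totals against the same inputs.**

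| Total | Per clinic (÷ 80) | Implied pre-loss requirement (÷ 1.25) | Bayley sessions (× 2) |
|---|---|---|---|
| 776 | 9.7 | 620.8 | 1552 |
| 800 | 10 | 640 | 1600 |
| 1200 | 15 | 960 | 2400 |

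The form's 388 per group would correspond to 388 / 1.25 = 310.4 per group before losses, a requirement the protocol does not state. Neither 776 nor 1200 follows from the sample size section.

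**3. Evaluable children after losses.** Adding 25% to 640 covers a loss of 1 − 640/800 = 20% of those enrolled. A loss of 25% of those enrolled would need 640 / 0.75, or 854 children.

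| Enrolled | Left at 20% loss | Left at 25% loss | Largest loss that keeps 640 |
|---|---|---|---|
| 776 | 620.8 | 582 | 1 − 640/776 = 17.5% |
| 800 | 640 | 600 | 20.0% |
| 1200 | 960 | 900 | 46.7% |

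At enrolment 776 exceeds 640 by 136. At the loss rate on which 800 rests, it ends about 19 short of 640.

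**4. What the 776 versus 800 gap does to power.** Assumptions, none stated in the protocol: two-sided 5% test, ICC from 0 to 0.10, design effect 1 + (m − 1) × ICC with m the evaluable children per clinic, and no gain from matching. The difference is 0.3 SD, as the protocol states.

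| ICC | 320 per group (m = 8) | 310.4 per group (m = 7.76) |
|---|---|---|
| 0 | 96.7% | 96.2% |
| 0.05 | 90.4% | 89.8% |
| 0.10 | 82.9% | 82.3% |

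The difference stays under one percentage point across the range.

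**5. What the 800 versus 1200 gap does to workload.** 1200 / 800 = 1.5, so 50% more children and 2400 − 1600 = 800 more Bayley sessions.

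**The case against.** The strongest reply is that the design section is not ambiguous. It is the only place that derives a number, the derivation is exact, and a methods section normally takes precedence over a form entry or a costing sentence. That stands, and it limits the point: the protocol does contain a usable target, so it would be too strong to say that nobody could judge later whether the target was met. Nor does any passage instruct field teams to recruit to 776 or 1200.

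A reader might also infer that the smallest total falls below the stated requirement. It does not. The 640 is the number before losses, and 776 is above it. The shortfall is conditional on losses above 17.5%. On a literal reading of 25% lost, the derived 800 would also fall short, at 600.

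The 1200 is a resourcing figure that occurs once and is not presented as an enrolment target. That is fair, but the sentence names the number of children to be tested in this study, and nothing explains why it is half as large again as the evaluation sample.

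Finally, one might infer from 4 testers in the narrative and 2 in the budget line that testing is underfunded. The documents do not support that. The table showing 2 totals USD 763,644, which equals the Grand Challenges Canada share in the Proposed Budget (383,004 + 380,640). The government share is a further USD 967,257 (711,931 + 255,326), and its full line items are not visible. The narrative also lists five Field Organizers against 3 in the same table, so it may cover posts funded elsewhere. The tester counts need reconciling and prove nothing more.

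**Conclusion.** The point holds as an inconsistency in current text: 776, 800 and 1200 are all given for the children to be evaluated or tested, and no passage reconciles them. Only 800 follows from the stated inputs. The largest total is 55% above the smallest (1200 / 776 = 1.55).

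The two discrepancies differ in weight. Between 776 and 800 there are 24 children, or 3%. That changes power by less than one percentage point under the assumed two-sided 5% level and ICC of 0 to 0.10, and matters mainly because the form and the design state different targets. Between 800 and 1200 there are 400 children and 800 test sessions, which affects workload and budget. The arithmetic rests on the protocol's figures alone; only the power comparison needs outside assumptions. Severity is moderate: the error does not threaten the planned comparison, but a sample size should have one value and correcting it is easy.

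**What to change.** State one enrolment number in the application form's evaluation table, the sample size section and the budget justification. The default is the derived 800: 400 per group, 10 children from each of 40 intervention and 40 control clinics, leaving 640 evaluable if losses are 20%. The loss rate should be stated with it, because 25% added is not 25% lost.

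If the sponsor intends 776 or 1200, the sample size section should be revised to derive that figure, including the number per clinic and the evaluable number it leaves. The documents do not show where 388 or 1200 came from, so the sponsor should confirm the intention before either is replaced.

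Also check the 4 testers in the budget justification against the 2 posts in the visible budget line, using the complete budget.

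Adopting 800 costs corrections to a form and a budget narrative, with no design change and no children beyond the 800 already derived. Adopting 1200 would mean 400 more children and 800 more test sessions than the current design.
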